#### Cost-effectiveness

Costs will be estimated by computing the average costs (using cost guideline provided by the National Health Care Institute) per individual based on the information collected by the NHR and in the interviews with hospitals. Since 2023, Dutch hospitals can claim costs of telemedicine using the National Health Care Institute’s Diagnosis Treatment Combination (DBC). This DBC can be used to estimate the average costs.^37^ A 95% credible interval (CE) will be computed using the percentiles of a Monte Carlo bootstrap analysis with 5000 resamplings. This average cost represents a sum of the costs of telemedicine use, inpatient days, days at intensive care unit, HF-related hospital procedures and outpatient visits. In a secondary analysis, we will re-estimate the average costs and 95% CE using data enriched with VEKTIS data (if linking is available), meaning that the costs of visits to the general practitioner, pharmacy and care at home are also taken into account.

Linkage with CBS may be incomplete for several participants because of missing values or incomplete data sets (eg, twins, different available time windows between registries of collected data). If the number of non-linked participants is below 10%, we will perform multiple imputation; if it is above 10%, we will perform HTA analysis on the complete subset.

Utility values will be estimated using the average hrQoL score collected in the HF registry and, if needed, from the literature. The difference in average QoL score between the group that uses telemedicine versus the group that does not represents the difference in disutility between the groups under the assumption that the collected hrQoL is a good representation of the utility of the particular health state that individuals were in.

Quality-adjusted life years (QALYs) are estimated by multiplying the observed number of follow-up years by the corresponding hrQoL score. Subsequently, the incremental cost-effectiveness ratio (ICER) is computed by taking the ratio between the difference of the costs of the average patient in the telemedicine group and those not in the telemedicine group, and the difference in QALY of both groups, thereby providing the cost per additional QALY gained. The 95% CEs are obtained using the Monte Carlo percentile methods described above. Both deterministic and probabilistic sensitivity analyses will be performed to completely outline uncertainty on individual and combined parameters in the model.

In addition, willingness-to-pay curves will be drawn to highlight the impact of different thresholds on cost-effectiveness outcomes.

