### Data collection and quality control

Data of the HF registry will be remotely monitored for major outliers and missing variables using the NHR; these processes have been described elsewhere.^30 35^ The NHR uses a unique individual patient identifier (NHRpersonID) to deduplicate registrations of the same patient (at the same or different hospitals) in the HF registry.^36^ During the RELEASE-HF study, researchers will perform an additional check on completed data and provide assistance to hospitals to reduce missing values, as well as assistance to reduce registration burden.

Telemedicine interviews, using an interview guide with closed-ended questions, will be performed by a RELEASE-HF investigator and conducted with clinicians (eg, cardiologist, HF nurse, nurse specialist, physician assistant). Interviews will be held during the 36-month period of data collection. All hospitals with telemedicine in HF care will be interviewed once, and the data will be checked with the hospitals once during the data collection period to be aware of changes in the components and status of telemedicine. For each hospital, the 6-monthly costs of telemedicine are determined via interviews and registration data (if at hand). The units will be linked to the unit cost guideline provided by the Dutch National Health Care Institute (Dutch: Zorginstituut Nederland).^37^ These interviews will be performed by a health technology assessment (HTA) scientist and conducted with clinicians or finance department staff. All participants will provide informed consent.

Patient-level telemedicine data are collected by a clinician, data manager or researcher at the hospital where the patient is being treated because these individuals have access to the identification log of the HF registry. Collected data will include the start date of telemedicine use and the frequency at which measurements are sent to the treating hospital, with a high rate typically referred to as a high-intensity (or acute) protocol and a low rate as a low-intensity (or stable) protocol.

The Heart4Data consortium will establish opportunities for data linkage between the HF registry and other national registry databases, in collaboration with public partners (figure 2).^28^ At the time of writing, a collaboration between these databases and the HF registry is not yet established for all external national databases.

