The primary outcome model is a linear mixed model with a random intercept for the participating centre and is specified as follows. The outcome is measured in days, and because the final measurement may be less or more than 365 days after baseline, we rescale the number of days of unplanned hospitalisation to the number of days under follow-up to 365 days. The outcome is computed by subtracting the days of unplanned hospitalisation or death from 365. The earlier described confounding variables are added to the primary outcome model to adjust for confounding. Continuous covariates are modelled using splines. Multicollinearity between confounding variables and the telemedicine status is evaluated. The coefficient for telemedicine in the primary outcome model represents the average treatment effect of offering any telemedicine within 3 months after HF diagnosis compared with not offering telemedicine on days with unplanned HF-related hospitalisation during a year in the population of patients with newly diagnosed HF. Robust SEs are estimated to compute CIs.

For the secondary outcome functional status, a similar approach is taken to estimate the average treatment effect of offering any telemedicine within 3 months after HF diagnosis compared with not offering telemedicine on functional status after 1 year in the population of patients with newly diagnosed HF. For this analysis, the outcome model is a multinomial regression model, and baseline functional status is added as a covariate. The risk difference relative to the reference outcome category is assessed using the predicted outcomes of the primary outcome model offering of telemedicine versus not offering, to obtain the marginal risk difference.^38–40^ Similarly, for the secondary outcomes health status and hrQoL, the outcome model is a probit regression model, with baseline measurements added as a covariate. Healthcare utilisation will be assessed using a Poisson regression model, and all-cause mortality will be assessed using binary logistic regression.

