##### Research question 2: effectiveness of different telemedicine components

Research question 2 investigates the effectiveness of the different forms of telemedicine intervention. We assess this question by performing three separate analyses in which intervention aspects are contrasted in the subset of participants that received telemedicine. The presence or absence of a telemedicine component is determined at a hospital level. The components of telemedicine that are contrasted are presence versus absence of a service centre, presence versus absence of an educational module, and high-intensity versus low-intensity protocol (table 2).

The population of interest is patients with newly diagnosed HF (maximum 3 months prior to baseline) who received telemedicine. Offering of telemedicine is measured at 6 months after baseline.

In addition to the set of confounding variables at the patient level used in the analysis above, confounding variables at the hospital level are considered because indication for telemedicine is expected to differ across hospitals. Confounding variables include academic or non-academic hospital, presence of a specialised heart centre, presence of an outpatient ward, size of outpatient ward (number of patients/year), staffing of the HF outpatient clinic and full-time equivalent of outpatient-ward staff.

For each of the three contrasts, the primary outcome model is fitted to estimate the average treatment effect of a component relative to the corresponding reference component on days of unplanned hospitalisation during 1 year in the population of patients with newly diagnosed HF that initiated telemedicine.

The secondary outcomes functional status, health status and hrQoL are assessed using similar approaches but using multinomial, probit and probit regression model, respectively. Healthcare utilisation and all-cause mortality will be assessed using Poisson regression model and binary logistic regression, respectively.

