##### Research question 4: cost-effectiveness of different telemedicine components

For research question 4, costs, utility, QALYs, ICER and willingness-to-pay curves will be computed to estimate the difference in cost-effectiveness between components of telemedicine, similar to the comparisons defined for research question 3 in the clinical effectiveness analysis.

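### The cost-effectiveness bootstrap names no hospital level although telemedicine components are hospital attributes; if patients are resampled, the research question 4 intervals will be too narrow whenever hospitals differ

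*Protocol article*

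**What the plan says.** The Cost-effectiveness section starts from a per-patient mean: "Costs will be estimated by computing the average costs (using cost guideline provided by the National Health Care Institute) per individual". Its uncertainty is given as "A 95% credible interval (CE) will be computed using the percentiles of a Monte Carlo bootstrap analysis with 5000 resamplings". For QALYs and the ICER it adds: "The 95% CEs are obtained using the Monte Carlo percentile methods described above". Neither this section nor those on research questions 3 and 4 mention a centre effect, a cluster or a hospital-level covariate.

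Research question 4 is to "estimate the difference in cost-effectiveness between components of telemedicine", using the comparisons from the clinical analysis. The cross-reference there gives research question 3, but the component comparisons are defined under research question 2. In that section, "The presence or absence of a telemedicine component is determined at a hospital level". The three contrasts are service centre, educational module and protocol intensity.

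Data collection and quality control says that telemedicine costs are determined for each hospital in six-month units, from interviews and, where available, registration data. The Cost-effectiveness section also permits a national claim code: "This DBC can be used to estimate the average costs".

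The clinical analysis does recognise hospitals: "The primary outcome model is a linear mixed model with a random intercept for the participating centre". It also uses robust standard errors, and research question 2 adds hospital-level confounders.

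**The concern.** When an exposure is constant within a hospital, the hospital is the independent unit of information about it. A bootstrap that draws patients one by one reproduces the sampling variation that would hold if patients in the same hospital were no more alike than patients in different hospitals. Admission practice, procedures, intensive care use and outpatient visits all enter the cost, and any of them can differ between hospitals for reasons unrelated to the component. A patient-level bootstrap leaves that variation out of the interval.

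Research question 4 is one of four stated objectives, and effective scenarios are to be proposed to hospitals nationally. Intervals and willingness-to-pay curves that are too tight would let a chance imbalance between a few dozen hospitals look like evidence that a component is, or is not, good value.

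**Working it through.** **Figures in the plan.** No precision or power is stated for the cost-effectiveness analysis, so there is no figure of its own to reproduce. The planned total is used below, and its last two steps are exact: 432 × 12 = 5184 and 5184 / 0.8 = 6480. The number of hospitals is at least 29 (Progress and time plan).

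**Assumed inputs (not in the documents).** ICC 0 to 0.05; the share of patients on telemedicine; hospitals of equal size; an even split of hospitals by component.

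**Telemedicine patients per hospital, m.** 6480 / 29 = 223 patients per hospital.
- 20% on telemedicine: 0.2 × 223 = 45.
- 50% on telemedicine after 20% losses at both the accrual and dropout steps: 6480 × 0.8 × 0.8 = 4147; 4147 × 0.5 / 29 = 72.
- 50% with no losses at all: 0.5 × 223 = 112, an upper case.
- 20: an illustrative low value, because research question 2 is restricted to newly diagnosed patients and the size of that restriction is not given.

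**Formulas**, for a difference in means on a hospital-level exposure:
- Design effect: DE = 1 + (m − 1) × ICC.
- Factor by which the standard error is understated: √DE.
- True error of a nominal 95% interval that ignores hospitals: 2 × [1 − Φ(1.96 / √DE)].

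Worked example, m = 72 and ICC = 0.02: DE = 1 + 71 × 0.02 = 2.42; √DE = 1.56; 1.96 / 1.56 = 1.26; error = 21%.

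| m | ICC 0 | ICC 0.01 | ICC 0.02 | ICC 0.05 | √DE, ICC 0.01 to 0.05 |
|---|---|---|---|---|---|
| 20 | 5% | 7% | 10% | 16% | 1.09 to 1.40 |
| 45 | 5% | 10% | 15% | 27% | 1.20 to 1.79 |
| 72 | 5% | 13% | 21% | 36% | 1.31 to 2.13 |
| 112 | 5% | 18% | 27% | 44% | 1.45 to 2.56 |

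**Check by simulation.** Skewed costs and no true component difference were simulated, with 600 runs of 400 bootstrap resamples and percentile intervals.
- Patients resampled, 29 hospitals: 9%, 16% and 29% for m = 45, and 19%, 27% and 46% for m = 112, at ICC 0.01, 0.02 and 0.05. These agree with the formula. At ICC 0 the result was about 6%.
- Hospitals resampled within component group: about 6–8% with 29 hospitals and about 8–11% with 15.

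The simulation covers mean costs. It did not simulate QALYs or the ICER.

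**The case against.** The article never names the resampling unit. The words about individuals describe how the mean cost is computed, and a condensed article may leave the unit to a fuller plan. This stands in part: patient-level resampling is an inference. But the article specifies the interval method down to the number of resamples, and it states the centre term for the clinical model. An ordinary bootstrap carried out as written would ignore hospitals.

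Four stronger readings are tempting, and the text does not support them:
- *The cost analysis has no model.* The section refers to parameters in a model for its sensitivity analyses but does not describe that model, so one cannot say what it omits.
- *One hospital cost is copied to every patient.* The article does not say how hospital costs are assigned. It links units to a national guideline, collects patients' start dates and measurement frequency, and allows a national claim code. A uniform tariff would, however, remove hospital variation only from the telemedicine item. Inpatient days, intensive care days, procedures and outpatient visits could still cluster.
- *The plan will declare false component differences.* No test or decision rule is attached to these intervals. The error rates above are the chance that an interval misses the true difference.
- *The same inflation applies to research question 3.* Users and non-users can occur in the same hospital, so this design effect does not carry over.

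It is also fair to say that clinical effectiveness is the stated primary focus, and that fewer eligible patients per hospital would shrink the problem.

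**Conclusion.** The point holds conditionally. If patients are resampled and the ICC is above 0, the research question 4 intervals are too narrow, and the willingness-to-pay curves share the fault. Over ICC 0.01 to 0.05, the coverage of a nominal 95% interval would fall to about 93–84% with 20 telemedicine patients per hospital, 90–73% with 45 and 87–64% with 72. With an ICC of 0 there is no loss. These figures rest on an assumed ICC, telemedicine share and even split over 29 equal hospitals, and they apply to differences in means rather than directly to the ICER. The inconsistency with the centre random intercept in the clinical analysis does not depend on those assumptions.

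**What to change.** In the Cost-effectiveness section, state that for research question 4 the bootstrap resamples whole hospitals within component groups, carrying along all their patients and their telemedicine cost. Use the same resamples for costs, QALYs, net benefit, the ICER and the willingness-to-pay curves.

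Add that with few telemedicine hospitals percentile intervals remain somewhat too narrow even then. A small-sample correction may be applied to cost and net-benefit differences. It should not be applied to the ICER, because the standard error of a ratio is unstable when the QALY difference is near zero. The performance of such a correction was not checked here.

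The cost is a sentence or two and a changed resampling unit in the code, with no new data. The downside is wider research question 4 intervals. The change corrects precision only: hospitals with and without a component may still differ systematically, and resampling hospitals does not adjust for that.

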#### National registries and databases

If legally and technically feasible, we plan to link the HF registry data, specific to RELEASE-HF, to external data sources to (1) complement missing variables, (2) enrich and validate the HF registry, and (3) reduce registration burden for healthcare professionals/data managers. The external data sources considered are Statistics Netherlands (CBS), the national health insurance database (VEKTIS), the national registry for hospital care (Dutch Hospital Data) and the national database for drug utilisation and drug safety (PHARMO). The variables of interest are visits to the outpatient clinic, to the emergency room and to the general practitioner related to HF, admission days at an intensive care unit, and treatment characteristics specific to HF (ie, medication as class of diuretics).

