### Sample size calculation

The primary focus in RELEASE-HF is on the clinical effectiveness of telemedicine in HF management. Hence, the sample size calculation is based on parameters relevant to this analysis. The sample size calculation was conducted in three steps: (1) computing the required sample size for the main effect of telemedicine on the primary outcome, (2) taking into account that subgroup effects are of primary interest and (3) anticipating the accrual rate.

For the first part, we assumed a mean increase in the number of days spent alive without unplanned hospitalisation of 6.4 (SD 21.1) days based on the findings of the TIM-HF2 study.^44^ This corresponds to a required sample size of 432 patients in total, based on a type I error probability of 5%, a type II error probability of 20% and accounting for 20% dropout.

Such a sample size would allow for an overall estimate of the difference between telemedicine and no telemedicine in days spent alive without unplanned hospitalisation in the overall patient population; however, our interest is in heterogeneous intervention effects. Hence, for the second part, the sample size was inflated to estimate subgroup effects.^50 51^ To detect interaction effects that are 50%–60% of the size of the overall effect (ie, increase of more than 3.2–3.8 days spent outside the hospital due to the interaction given the main effect) with a power of 80%, the required sample size is inflated by a factor of 12.^50^ This results in a required sample size of 5184 individuals.

Finally, from the HF registry pilot study (CHECK-HF), we know that, in view of the estimated average number of patients per hospital, the average proportion of included outpatient clinic patients with HF was above 80%.^52^ Taking this accrual rate into account, we would require the inclusion of 6480 patients with HF.

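### The CBS non-linkage rule runs the wrong way: it imputes below 10% non-linked and drops to complete cases above 10%, where selection bias in linked economic data can be largest

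*Protocol article*

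**What the plan says.** The rule stands in the Cost-effectiveness section of the protocol article. It starts from the expectation that "Linkage with CBS may be incomplete for several participants because of missing values or incomplete data sets", with twins and differing time windows between registries as examples. Two branches follow: "If the number of non-linked participants is below 10%, we will perform multiple imputation"; and "if it is above 10%, we will perform HTA analysis on the complete subset". No reason is given for the cut-off or its direction, and exactly 10% is not covered. The sensitivity analyses announced in the same section concern the uncertainty of model parameters, not selection through non-linkage.

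Three other statements bear on how far the rule reaches:

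- Average costs are to be estimated "based on the information collected by the NHR and in the interviews with hospitals". Enrichment with health insurance data (VEKTIS) is a secondary analysis. Utilities come mainly from quality-of-life scores in the HF registry.
- Linkage is conditional: "If legally and technically feasible, we plan to link the HF registry data". The section National registries and databases lists intensive-care days and outpatient visits among the variables sought externally, without saying which source supplies which variable.
- Table 1 gives an external data source as one origin of the cost outcome.

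**The concern.** A complete-case analysis does little harm when few records are missing and can do much when many are. The rule reserves the more protective method for the easy case and the weaker method for the hard one.

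Unlinked patients are not empty records. The HF registry still holds their baseline characteristics, heart failure admission days, quality-of-life scores and mortality. Restricting the analysis to the complete subset would discard these because a different source failed to link, although they are what an imputation or weighting model would use.

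At stake are the costs and incremental cost-effectiveness ratios for research questions 3 and 4, so far as they draw on linked variables. QALYs are at stake as well if the restriction is applied to the whole health-economic analysis.

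**Working it through.** **The plan's own figures.** The 10% cut-off has no derivation to reproduce. The planned cohort, used here only for scale, does reproduce. The inputs are a "mean increase in the number of days spent alive without unplanned hospitalisation of 6.4 (SD 21.1) days" and a "type I error probability of 5%, a type II error probability of 20% and accounting for 20% dropout". Per arm, 2 × (1.96 + 0.84)² × 21.1² / 6.4² gives 171, so 342 in total, and 342 / 0.80 = 428 (430 with the t distribution) against the stated 432. Then 432 × 12 = 5184 and 5184 / 0.80 = 6480, which matches "we would require the inclusion of 6480 patients with HF".

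**Where the rule switches.** 10% of 6480 is 648. With 647 unlinked patients all are kept and imputed. With 649, all 649 are dropped and 6480 − 649 = 5831 remain. At exactly 648 the rule is silent.

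**Bias of a complete-case mean.** Let m_L and m_U be the mean cost of linked and unlinked patients in a group, u the unlinked share, and d = m_L − m_U. The full mean is (1 − u) m_L + u m_U, so

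bias = m_L − [(1 − u) m_L + u m_U] = u × d.

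The standard error, relative to fully observed data, grows by 1/√(1 − u).

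| u | Unlinked of 6480 | Linked | Complete-case bias | SE factor | What the rule does |
|---|---|---|---|---|---|
| 5% | 324 | 6156 | 0.05d | 1.03 | imputes |
| 9% | 583 | 5897 | 0.09d | 1.05 | imputes |
| 11% | 713 | 5767 | 0.11d | 1.06 | drops |
| 20% | 1296 | 5184 | 0.20d | 1.12 | drops |
| 40% | 2592 | 3888 | 0.40d | 1.29 | drops |

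For a fixed d, both columns rise with u. The complete-case method is used only in the range where they are largest.

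**Bias of the incremental cost.** With subscripts 1 and 0 for telemedicine and no telemedicine, the bias is u₁d₁ − u₀d₀. It vanishes when selection is the same in both groups. With 20% unlinked in one group, 10% in the other and the same d, it is 0.20d − 0.10d = 0.10d.

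**Size in money terms.** The article gives no figure for d. As an assumed range, let unlinked patients cost between the same as linked patients and 30% more. The understatement of the mean, as a share of the true mean, is then:

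- at 15% unlinked: from 0 to 0.15 × 0.30 / 1.045 = 4.3%;
- at 30% unlinked: from 0 to 0.30 × 0.30 / 1.09 = 8.3%.

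If unlinked patients were cheaper, the sign would reverse.

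**Simulation.** The setting was N = 6480, 100 replicates and 5 imputations. By assumption, missingness depended on an observed covariate (log-odds slope 1 per SD) correlated 0.71 with cost. Complete-case bias in SD units was −0.06 at 9% unlinked, −0.07 at 11%, −0.12 at 20% and −0.23 at 40%. With imputation it was 0.00 throughout. That zero follows from simulating data that are missing at random. It shows what imputation can do, not what it would achieve here.

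**The case against.** Several points on the other side carry weight.

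- **Reach.** A reader might infer that all costs, QALYs and cost-effectiveness ratios would come from a selected subset. The article does not support that. Base costs are attributed to registry data and interviews, utilities come mainly from the registry, and the rule concerns CBS linkage, which may never happen. But the rule speaks of the HTA analysis without confining it to the secondary analysis, and two components of the base cost, intensive-care days and outpatient visits, are also sought externally. The reach is ambiguous, not nil.
- **Cause of non-linkage.** A reader might infer that differing time windows follow calendar time and hence telemedicine roll-out. The article does not say so, and twin status is plausibly unrelated to cost. What remains is that differing time windows make purely random non-linkage doubtful.
- **Size.** The 30% difference is an assumption, and zero bias lies within the range. The SE factors compare with fully observed data, so they overstate what imputation would regain.
- **The threshold itself.** Fixing a cut-off on the linkage rate in advance is ordinary contingency planning and creates no bias by itself. The fault is the direction of the switch.
- **Imputation at high missingness.** Non-linkage removes a whole block of variables, and imputing a large share leans heavily on the model. That could justify leaving imputation at some point. It does not justify complete cases at just over 10%, where the full cohort can still be analysed with registry and interview costs.

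**Conclusion.** The point holds as a flaw in a rule that the article itself fixes, within the economic analyses only. Above 10% non-linkage the plan takes away protection against selection, just where the possible bias of a group mean passes 0.10d and rises to 0.20d at 20% and 0.40d at 40%.

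Actual bias in mean cost requires non-linkage to be related to cost. Bias in the incremental cost also requires that selection differ between the telemedicine groups. The article establishes neither the presence nor the absence of these conditions, so the size of any error is unknown and may be zero.

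The primary clinical outcome is derived from the HF registry and is not governed by the rule. The change is worth making because it is cheap, but the validity of the main study does not depend on it.

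**What to change.** Delete the switch to complete cases at 10% and put the following in its place.

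- At any level of non-linkage, use multiple imputation of the linked variables, or inverse-probability-of-linkage weighting. The model should contain telemedicine exposure, registry outcomes, the listed confounders, hospital and calendar time, and should be combined with the planned bootstrap.
- Keep the registry-based costs and QALYs of all patients, linked or not.
- Compare linked with unlinked patients by telemedicine group, and report the complete-case result as a sensitivity analysis.
- If non-linkage is too large for credible imputation, rely on the registry-plus-interview cost analysis in the full cohort, which the Cost-effectiveness section already describes.
- State which cost components depend on linkage, so that the reach of the rule is clear.

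The cost is a few sentences of plan text and extra computing, since imputation must be combined with 5000 resamplings. The real price is reliance on data being missing at random given the model, so a sensitivity analysis should let unlinked patients' costs depart from that assumption.
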